**Design**

A randomized, controlled, clinical trial will be conducted in accordance with the ethical principles governing research involving human subjects stipulated in Resolution 466/2012 of the Brazilian National Board of Health. The study received approval from the Human Research Ethics Committee of the *Faculdade Evangélica Mackenzie do Paraná* (process number: 37083714.0.0000.0103; certificate number: 3.580.973) and the protocol was registered and approved on the Rebec platform, trials RBR-3JMX67. All patients agreed to participate by signing a statement of informed consent.

A person participant of the team, not directly involved in the research, will be responsiblefor obtainingthe signatures oftheconsentforms of patients which were initially selected as potential participants in the trials.

**Study population**

Forty patients with a diagnosis of HSP will be recruited from the hospital of the Federal University of Parana in the city of Curitiba, Brazil. To participate, the volunteers must meet the following eligibility criteria:

**Inclusion criteria**

Age 18 years or older (with no restriction imposed regarding maximum age);

Men or women with HSP.

**Exclusion criteria**

Otologic condition that could affect the vestibular examination;

Use of gait-assistance device;

Inability to understand simple verbal commands;

Significant musculoskeletal condition that could impede the assessment and VR;

Severe visual impairment or other abnormality that could impede the proposed procedures.

Eligible patients will undergo the following:

**Patient history**

Patient histories will be taken with an emphasis on otoneurological signs and symptoms;

**Otolaryngologic evaluation**

The aim of the otolaryngologic assessment is to exclude individuals with any abnormality that could interfere with the study;

**Vestibular assessment**

Subsequently, they will carry out the evaluation by the physiological profile (PPA) and Lafayette dynamometer, and application of 10 questionnaires / scales described below before the rehabilitation (1st evaluation) and after the 20th rehabilitation session 2nd assessment), to observe the post- intervention.

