**Randomization**

Prior to the intervention, the volunteers will be randomly allocated to two different groups. Randomization will be performed by an independent researcher using a simple lottery system with sealed opaque envelopes immediately after the baseline assessment. The volunteers will be considered participants in the study the moment the envelope is opened. The participants will be randomized to receive the following distinct interventions:

Group I: Twenty volunteers will undergo VR with virtual reality (balance games) using the Wii® console, Wii-Remote and Wii Balance Board (Nintendo).

Group II: Twenty volunteers will undergo VR with virtual reality (balance games and muscle strength games) using the Wii® console, Wii-Remote and Wii Balance Board (Nintendo).

The games will last from 30 minutes to one hour, with sessions twice a week for 10 weeks (total: 20 sessions).

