**Treatment**

All participants will receive orientation regarding the rehabilitation procedure. The VR will involve virtual reality with the use of the Wii Fit Plus®, Wii-Remote and Wii Balance Board (Nintendo). The Wii Balance Board (WBB) is a platform with sensors that detect the position and orientation of the gamer. In some games, the player must perform the same movement he/she would do in a real game. The VR with virtual reality games will be performed in both groups for 30 minutes twice a week for a total of 20 sessions. Group I will play five balance games. Group II will play the same five balance games plus four strength games. The games will be selected to favor changes in balance and postural instability. After completing the collection of all data, to ensure the same rehabilitation for both groups, will be available the training with strength exercises to group I.

The following are the balance games performed on the WBB:

Soccer Heading®

Table Tilt®

Tightrope Walk®

Penguin Slide®

Perfect 10®

The muscle strengthening exercises were selected to improve balance, which depends on the interaction between vision, vestibular and peripheral sensations, central commands and neuromuscular responses:

Single leg extension®

Torso Twist®

Sideways Leg Lift®

Single Leg Twist®

The training phases will be performed simultaneously, avoiding complications and alterations that may compromise the validity of training. The assessment will be performed again after the 20 intervention sessions.

The time schedule of enrolment, interventions, assessments and visits for participants are describe in Table 2 in accordance of Spirit checklist (Figure 1)

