**Management**

The researches ensure that the anonymous character and the confidentialityof participants, dealing with people or data files, will be maintained and their identities or any kind of identification will be protected. The clinics records, research instruments or any document that can be used, containing data of participants, will not be identified by the name, but through a code, even when submitted to regulatory institutions or sponsors. Researchers willmaintain the record of inclusion of participants confidentially, containing codes, names and addresses for their own use. The files of the Consent forms will be issued in two copies each one of them to be known and signed by participants, researchers and researched (or legal representatives), the files will be maintained by the researcher in strict confidence, all together, in a single file related to that research. We ensure that participants that comprise the casuistry will receive an original copy of the Consent term.

There is no personal expense for the participant in any stage of the study, instead, all assessment shall be free, including the otorhinolaryngological evaluation, PPA and dynamometer. There is also no financial compensation related to your participation. If there is any additional expense, it will be absorbed by the research budget. Participation in this study is completelyvoluntary and non-participation does not imply any change in your medical follow-up, not even will change the relationship between the team and the patient. After signing the Consent term, you will have total liberty to take it out at any moment and leave participatingin the study, if desired, without any damage to the development of the treatment and follow-up at the institution.

The results of this research may be presented in at meetings or publications, however, your identity will not be revealed in these presentations.

The risks during the research are minimal or non-existent, but the realization of the assessment and rehabilitations may cause discomfort, arising from the direct interference on the vestibular system responsible for the balance. The support in this sense may be momentary interruption of the evaluation VR, until medical interventions if necessary. However, if persists the discomforts the participant will be removed from the research and the data collected will be excluded from the sampling, and the patient will not be reallocated in any group.

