**Assessment of results**

The participants will be evaluated by an independent examiner who will be blinded to the allocation to the different groups. The primary outcomes will be evaluated with each of the assessment tools, considering an improvement in the performance in the comparison of the pre-intervention and post-intervention assessment:

PPA: quantifies the risk of falls.

Dynamometer: verification of improvement in muscle strength;

WHOQOL-Bref: improvement in perceived quality of life in different domains;

BBS: analysis of balance status;

ABC: like BBS, verifies balance, but related to activities of daily living;

VADL: investigates impact of dizziness and balance on degree of dependence;

MMSE: measures degree of cognitive impairment;

TUG test: measures risk of falls related to muscle weakness;

FES-I: investigates fear of falling;

VAS: quantifies pain intensity.

The secondary outcomes will quantify the improvement in performance on the assessment. For such, a specific questionnaire will be administered for each assessment.

Secondary outcome 1: Improved locomotion capacity, increased stability during gait, reduction in gait deviations; evaluated using TUG test and BBS.

Secondary outcome 2: Increased spatial orientation capacity; evaluated by PPA, WHOQOL-Bref, ABC scale and MMSE.

Secondary outcome 3: Reduction in falls;evaluated by FES-I, ABC scale, VADL scale and dynamometer.

Secondary outcome 4: Improved capacity to perform activities of daily living, generating self-confidence that will lead to positive gains in aspects of family, social and professional life; evaluated by WHOQOL-Bref, VAS and VADL scale.

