**Data analysis**

Data analysis will involve repeated-measures ANOVA with the level of significance set at 5%.

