**Control of bias**

The study includes several important methodological resources that will minimize the risk of bias, such as the randomization process, allocation concealment, blinded assessment of the results and intention-to-treat analysis.

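### The only follow-up assessment is tied to the 20th session, so randomised participants who stop early or fall behind have no scheduled outcome, contrary to the claimed intention-to-treat analysis

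*Protocol*

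**What the plan says.** The Protocol sets the second assessment by session count in two places. Vestibular assessment places the measurements "before the rehabilitation (1st evaluation) and after the 20th rehabilitation session". Treatment repeats it: "The assessment will be performed again after the 20 intervention sessions". Neither gives a calendar date or a window.

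The planned programme, under Randomization, is "with sessions twice a week for 10 weeks (total: 20 sessions". This describes treatment delivery. It gives no rule for missed sessions and no assessment for anyone who stops early.

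Four other statements bear on the point:

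- Randomization: "The volunteers will be considered participants in the study the moment the envelope is opened". Participation therefore begins before any session is delivered.
- Assessment of results: outcomes are judged by "considering an improvement in the performance in the comparison of the pre-intervention and post-intervention assessment".
- Data analysis: the method is a repeated-measures ANOVA at the 5% level, with nothing on missing second values.
- Control of bias: the listed safeguards include "blinded assessment of the results and intention-to-treat analysis".

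For persistent discomfort, Management says that "the participant will be removed from the research and the data collected will be excluded from the sampling".

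**The concern.** Intention-to-treat needs an outcome, or at least a planned attempt to obtain one, for everyone randomised. Here the attempt depends on something that happens after randomisation, namely reaching session 20. If the text is followed to the letter, the people who can be analysed are those who completed the programme.

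The Protocol itself foresees early stopping. Participants may leave at any time, discomfort may lead to removal, and telephone contact is planned to support adherence. The arms also differ in content (five balance games against the same five plus four strength games), so unequal completion is possible. If completion is related to how well a participant is doing, a comparison of completers no longer has the protection of randomisation.

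A second effect is timing. If sessions are missed and made up later, the interval between the two assessments depends on attendance. The Protocol describes the disease as slowly progressive, so the interval should not be left to vary without record.

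**Working it through.** **1. Reproduce the plan's own figures.** 2 sessions per week × 10 weeks = 20 sessions, and 20 + 20 = 40 participants. Both agree with the Protocol. It states no power, effect size, SD or non-completion rate, so everything from step 3 on rests on assumed inputs.

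**2. Set the statements side by side.**

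| Section | What it implies for someone who stops at, say, session 12 |
|---|---|
| Randomization | Is a participant, counted from the opening of the envelope |
| Vestibular assessment; Treatment | The trigger for the second assessment is never reached |
| Assessment of results; Data analysis | A pre-post pair is needed, and only the first value exists |
| Control of bias | Should be in the analysis |
| Management | If removed for persistent discomfort, collected data are excluded as well |

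A two-occasion repeated-measures ANOVA in its usual form uses only participants with both values. A mixed model would keep the baseline value, but a person without a second value adds almost nothing to the group-by-time contrast.

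**3. Timing (assumed attendance).** Suppose each scheduled session is attended independently with probability p. The chance of all 20 within 10 weeks is p^20. If missed sessions are made up at the same pace, the mean time to session 20 is 20/(2p) weeks.

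| p | p^20 | 20/(2p) |
|---|---|---|
| 0.95 | 36% | 10.5 weeks |
| 0.90 | 12% | 11.1 weeks |
| 0.80 | 1% | 12.5 weeks |

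So session 20 coincides with week 10 only with perfect attendance. The Protocol does not mention make-up sessions. Without them, the 64% to 99% with at least one missed session (100% minus the middle column) would never reach the trigger.

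**4. Bias (assumed loss of 3 of 20 in one arm, none in the other).** For 20 independent normal responses, the three lowest expected values sum to about −4.41 SD. Removing exactly those three raises the mean of the remaining 17 by 4.41/17 = 0.26 SD. If non-completion is correlated ρ with response, the shift is about ρ × 0.26:

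- ρ = 0: 0 SD
- ρ = 0.5: 0.13 SD
- ρ = 1: 0.26 SD

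The direction favours the arm that loses its poorer responders.

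**5. Precision (assumed 15% loss in both arms).** 20 × 0.85 = 17 per arm. The confidence interval widens by √(20/17) = 1.085, about 8%.

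**6. Scale.** At 80% power and two-sided 5% (power and sidedness assumed), the detectable difference is (1.96 + 0.84) × √(2/n): 0.89 SD with n = 20 and 0.96 SD with n = 17. The trial has little precision to spare.

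**The case against.** A reader might infer that the Protocol leaves non-completers unmeasured by design and has in effect chosen a completers' analysis. The documents do not support that. No sentence says that people who stop early will not be assessed. The reference to session 20 can be read as shorthand for the end of a 10-week programme, and the assessment is elsewhere simply called post-intervention. The Treatment section also refers to a schedule table and figure that are not shown and could carry a week-based time point. What stands is narrower: both text statements use the session count, no other visit is described, and the text would need reconciling with the schedule even if that does give a week.

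A second objection is that handling of missing values belongs in a statistical analysis plan, which may exist. That is fair for imputation or the choice of model, and the missing-data method is no part of this point. But an analysis plan cannot recover a measurement that was never scheduled, and visit timing is a protocol matter.

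A third concerns size. Loss in one arm only, and its link with response, are assumptions. Nothing in the Protocol shows that tolerance differs between arms; both have the same number and frequency of sessions, and adherence support is planned. It would be wrong to read 0.13 to 0.26 SD as the expected bias. The range starts at 0, and its upper end requires that exactly the three worst responders leave.

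Finally, a fixed date does not secure data from people who withdraw consent, so some loss of precision may remain.

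**Conclusion.** The point holds as a conflict within the Protocol. The only post-baseline assessment described is conditional on the 20th session, while the analysis needs a pre-post pair and is claimed to be by intention-to-treat. Followed literally, early stoppers are unmeasured and those who fall behind are measured at a different interval, if at all. The exclusion of data stated under Management is a separate and explicit contradiction of the same claim, and it adds to the conflict.

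The size cannot be determined from the document. Under the stated assumption of 3 of 20 lost in one arm, the bias lies between 0 and about 0.26 SD, with 0.13 SD at a correlation of 0.5. A 15% loss in both arms costs about 8% in interval width. Make-up sessions and unequal adherence are possibilities, not facts of the plan. This is something the sponsor should correct, because the remedy is specific and cheap and the safeguard it protects is one that the Protocol relies on.

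**What to change.** - In Vestibular assessment and Treatment, time the second assessment from randomisation: the end of the planned 10-week programme period, with a stated window. Apply it to every randomised participant who has not withdrawn consent, whatever number of sessions they attended.
- Analyse participants as randomised. Report sessions attended and actual assessment timing by arm.
- Reconcile Vestibular assessment, Treatment, Management, Control of bias and the schedule table, so that they agree on who is assessed, when, and whose data are kept.
- Flag any late assessment of participants who have already stopped as outside the window, and examine its influence in a sensitivity analysis. Such assessments bring back a variable interval and should not be pooled without comment.

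The change alters assessment timing only, not treatment. It costs a few extra assessments by the same blinded examiner, and some participants will be measured before finishing 20 sessions, which is consistent with intention-to-treat. The Timeline section says that recruitment is complete and treatment was expected to end by July 2021. Some participants may therefore already have been assessed under the session-count rule, which is a further reason to report timing by arm.

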**Physiological Profile Assessment**

The physiological profile assessment (PPA) is a validated assessment tool for the risk of falls developed by Lord, Menz and Tiedemann *et al*.^12^. Performs direct assessment of sensory motor skills. The score indicates the degree of risk: <0 = low risk, 0-1 = mild risk; 1-2 = moderate risk; and> 2 = high risk of falls, indicating the individual's performance in comparison to the normative values for each age group.

**Lafayette dynamometer**

The Lafayette dynamometer^13,14^ is a portable device for the objective quantification of muscle strength based on the assessment of maximum voluntary isometric contraction^15^. Applicable to all segments of the body, measures peak force, duration of peak force, force (kgf) between selected intervals, mean force, total test time and peak torque.

**Quality of life**

The Quality of Life Group of the World Health Organization (WHO) developed the short version of the WHOQOL-100 denominated the WHOQOL-Bref ^16^. This version is a useful alternative to the long version, as the proposed study will involve several assessment tools. The questionnaire is used to determine the perceptions of individuals about your health and can be used to assess the quality of life of different populations and in different situations^17.^

**Berg Balance Scale (BBS)**

The Brazilian version of the BBS, which was cross-culturally adapted to the Brazilian population by Myamoto *et al.*^18^, will be used to determine risk factors for the loss of independence and falls. The maximum score is 56 points, with higher score denoting better balance. The score is analyzed to determine the degree of the risk of falls: low, medium, high or 100% risk.

**ABC Activities-Specific Balance Confidence (ABC) scale**

The ABC scale, translated and adapted to the Brazilian population^19^, showing good quality, discriminating validity, consistency and reliability^20^.It has 16 items for assessing balance during a set of activities of daily living (ADLs) of medium difficulty^21^. The confidence for each ADL is measured by the volunteer, choosing a percentage point on a scale ranging from 0% (without confidence) to 100% (total confidence). A total greater than 80% corresponds to a high functional level, 50 to 80% moderate physical functioning and a score below 50% indicates a low functional level^22^.

**Vestibular Disorders Activities of Daily Living (VADL) scale**

The VADL scale was developed by Cohen and Kimball^23^ to assess the impact of dizziness and imbalance on the performance of activities of daily living among individuals with vestibular disorders. The scale involves 28 activities divided into three dimensions: functional, locomotion and instrumental. The total VADL and dimension scores are determined by the median of the activity scores, with higher scores denoting greater dependence and disability^24^. The translation of the VADL from English into Brazilian Portuguese was performed following the guidelines of the Process of Cross-Cultural Adaptation^25^.The Brazilian version had adequate reliability and is a new assessment tool in the country for investigating functional capacity in individuals with vestibulopathies as well as guiding therapeutic planning, particularly vestibular rehabilitation^26^.

**Mini Mental State Examination (MMSE)**

The MMSE is a fast, short, 30-item measure to screen for cognitive impairment^27^ that addresses spatiotemporal orientation, immediate recall and word evocation, calculation, naming, repetition, executing a command, reading, writing and visuomotor skill^28-30^.The MMSE items were categorized by Folstein *et al*.^27^into five dimensions based on theoretical analysis and clinical practice. The Brazilian version of the MMSE was adapted by Brucki *et al*.^29^, who described the adaptations for the use of MMSE in Brazil and proposed rules to standardize its application for the detection of cognitive loss in the follow up of disease and monitoring of the response to treatments. The measure received the denomination “mini” because it focuses on only the cognitive aspects of mental function, excluding mood and abnormal mental functions^27^.It provides information on different cognitive variables^31^, containing items grouped into seven categories, each of which is designed to evaluate specific cognitive functions. The total ranges from 0 points (severe cognitive impairment) to 30 points (best cognitive performance).

**Timed Up and Go (TUG) test**

According to Paula, Alves Jr. and Prata^32^, the TUG test consists of standing up from a chair without using the arms, walking three meters, turning around, walking back to the chair and sitting down again. The test begins and ends with the volunteer seated with the back against the backrest of the chair. The volunteer begins with the command "go" and the time needed to complete the task is timed with a stopwatch. According to the literature, there is no consensus on the results of this test. However, Guimarães *et al*.^33^ established the following markers: less than 10 seconds to complete the TUG test indicates a low risk of falls; 10 to 20 seconds indicates a medium risk and more than 20 seconds indicates a high risk of falls.

**Falls Efficacy Scale – International (FES-I)**

The FES-I is a self-administered questionnaire designed to evaluate the fear of falling during a set of activities. It is composed of 16 items scored from 1 to 4 points, with higher scores denoting a great fear of falling during a given activity. The FES-I has internal consistency of 0.96. Moreover, most items enable differentiating individuals who have suffered a fall, those who have suffered two or more falls and those who have not fallen^34^.The version validated for the Portuguese language will be used^35^.

